***Study population***

The study population is defined as students aged 12-16 years moving from year 8 into year 11 during the trial. The majority of these students will have received the intervention in years 9-10. This age-group is targeted because: proximal risk factors for adverse sexual health outcomes are manifesting,(49) prevention is not too late; and RSE is acceptable.(37, 50, 51) PPI suggests provision to year 11 students is unfeasible because of GCSE preparation. Outcomes will be analysed among students reporting data at 33-month follow-up with any missing baseline data on socio-demographic characteristics or age of sexual debut being imputed based on responses at follow-up. No students deemed competent to consent by schools will be excluded from research recruitment and consent procedures unless parents withdraw them from the research. Those consenting to participate who have mild learning disabilities or limited English will be supported to complete the questionnaire by researchers.

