***Analytic sample and sample size***

We calculate that, for 80% power with 5% significance, conservatively assuming: a sample of 140 students per school; drop out of 2 schools per arm; 80% student survey response rate at follow-up; an intra-cluster correlation coefficient (ICC) of 0.015 for our primary outcome; and prevalence of this outcome of 9% among those in the control arm, we will require 25 schools per arm to detect a 36% reduction in the primary outcome (giving a prevalence of 5.85% in the intervention arm). The minimum analytic sample for outcome assessment in the RCT will therefore be approximately 6440 students providing follow-up data at 33 months. Repeating this power calculation for the originally intended primary outcome of conceptions (where the prevalence among female controls would be around 2%)(13) would require >100 schools per arm.

These estimates are informed by research and PPI. We assume 140 students per school informed by our recent INCLUSIVE trial.(52) This is a conservative assumption for the Positive Choices trial because the average year group has now risen to 190 and so assuming an 80% response rate (again informed by the Positive Choices pilot and previous studies(42, 52-54)) this would comfortably provide over 150 students.(55) Two schools dropping out is also a conservative assumption given our previous trials have experienced no drop outs.(42, 52, 53) Regarding ICCs, no data are available on school-level clustering of lack of sexual competence at first sex but we would expect this to be very similar to ICCs for non-use of contraception at first sex, which are reported as 0.01(56, 57) so a conservative assumption of 0.015 for this study is reasonable.

Our assumption about prevalence of the primary outcome among controls is also informed by the literature. Around 25% of 15-16 year-olds are sexually active compared with 7% of 12-13 year-olds.(58) Therefore, between baseline and follow-up, we would expect 18% of students to become sexually active. Data from young people participating in the third Natsal sexual behaviour survey suggest that, among those aged 15-16 years, around half lack sexual competence at first sex.(1, 2) Therefore, we would expect around half of trial participants who become sexually active by follow-up (i.e. 9% of all participants) will experience non-competent sexual debut.

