
Secondary outcomes will examine other important potential benefits:

- age at sexual debut, using an adapted version of the RIPPLE measure;(72)
- non-use of contraception at first and last sex among those reporting heterosexual intercourse, using an adapted version of the RIPPLE measure;(72)
- number of sexual partners, using an adapted RIPPLE measure;(72)
- dating and relationship violence (DRV) victimisation (including non-volitional sex) measured using an adapted version of the short Conflicts in Adolescent Dating Relationships Inventory (sCADRI) scale which is widely used and was piloted for reliability in our recent Project Respect study (ordinal alpha=0.89);(42, 73, 74)
- sexually transmitted infections (STIs), focused on self-reported diagnosis with common infections, using an adapted version of the RIPPLE measure;(72)
- pregnancy and unintended pregnancy for girls and initiation of pregnancy for boys using adapted versions of the RIPPLE measures.(72)

*Intermediate outcome measures:* We will not undertake mediation analysis because this requires two waves of follow-up, which is not planned in the interests of minimising costs and maximising school retention. It is our experience across studies that multiple follow-ups reduce rather than maintain school engagement and hence response rates.(52) However, informed by our theory of change,(64, 65) we will undertake exploratory analyses of intervention effects on the following ‘intermediate’ outcomes(75) using existing measures(36, 39, 51, 76) tested for reliability in our pilot (ordinal alphas indicated below for multi-item scales): school-level social norms supportive of healthy relationships and sexual health (alpha=0.77); individual-level attitudes towards DRV (alpha=0.65) and gender roles (alpha=0.68); individual-level school engagement (alpha=0.74); career/educational aspirations; sexual health knowledge (alpha=0.78); sexual health and contraceptive skills (alpha=0.92); sexual communication self-efficacy (alpha=0.93); and communication with parents; sexual and reproductive health services access (alpha=0.83) DRV perpetration (including non-volitional sex) measured using sCADRI (ordinal alpha=0.88); and sexual harassment.(77)

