A statistical analysis plan will be drafted by the CTU and a data dictionary by the fieldwork team. Statistical analysis of survey data will be led by the CTU, with analysis of fidelity data by the fieldwork team and economic data by [name]. School randomisation and retention, and student response rates will be described using a CONSORT diagram.(88) Baseline and follow-up data will be tabulated by arm. Continuous outcomes will be summarised for each trial arm using means and standard deviations and binary outcomes will be summarised for each trial arm using numbers and percentages. We will conduct intention-to-treat analyses of primary and secondary outcomes (88) as well as exploratory analyses of our intermediate outcomes (RQ1) to estimate intervention effects, reporting 95% confidence intervals and P values for primary and secondary outcomes but not for exploratory analyses of the intermediate outcome. The analytic sample will be students providing follow-up data at 33 months. Analyses will account for school clustering. All outcomes will be analysed using generalised estimating questions (GEEs) with an exchangeable correlation structure and the sandwich estimator of variance to adjust for clustering, with small sample bias correction for the degrees of freedom. For binary outcomes GEEs will be fitted, with a log link to estimate risk ratios and identity link to obtain risk differences. In the event of low prevalence resulting in non-convergence of the GEE model a hierarchical modified Poisson regression model will be used to obtain risk ratios, followed by marginal standardisation to obtain risks for calculating risk differences where required. For continuous outcomes GEEs with an identity link will be used to obtain mean differences.

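### Age at sexual debut falls by default to a GEE mean difference, computable only among students who have debuted; this can hide, shrink or reverse a true delay

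*Combined protocol and SAP*

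**What the plan says.** Under Outcome measures, the first secondary outcome listed is "age at sexual debut, using an adapted version of the RIPPLE measure". No variable type is given, and the measures table in Supplementary Materials 3 does not include the item.

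Data management and analysis then states: "All outcomes will be analysed using generalised estimating questions (GEEs) with an exchangeable correlation structure". Two branches follow. One reads: "For binary outcomes GEEs will be fitted, with a log link to estimate risk ratios and identity link to obtain risk differences". The other reads: "For continuous outcomes GEEs with an identity link will be used to obtain mean differences". No time-to-event model or censoring rule appears. The same section promises intention-to-treat analysis of secondary outcomes, with confidence intervals and P values, and defines the population: "The analytic sample will be students providing follow-up data at 33 months".

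The sample size section gives the debut figures: "Around 25% of 15-16 year-olds are sexually active compared with 7% of 12-13 year-olds", and so "between baseline and follow-up, we would expect 18% of students to become sexually active".

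The only data-handling rule that names this variable, under Study population and again under Minimising bias, concerns "any missing baseline data on socio-demographic characteristics or age of sexual debut being imputed based on responses at follow-up". It says nothing about students who have not debuted.

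**The concern.** A student who has not had sex by the follow-up survey has no age at debut; the value is right-censored. A mean difference has to leave that student out. The comparison is then between debuters in each arm, a subgroup defined by an event that the intervention is meant to influence, and it omits the students in whom a delay succeeded best.

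A second problem arises if debuts before baseline are counted, which the plan neither states nor excludes. The intervention cannot change those debuts. They are the youngest ages, and their share among debuters grows as later debuts are prevented. That pulls the intervention-arm mean down.

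The Background cites delayed debut as a benefit of whole-school programmes. An effective intervention could therefore show no effect on this outcome, or an apparently earlier debut.

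**Working it through.** **The plan's own figures.** 25% - 7% = 18% debut between baseline and follow-up, as stated. Not debuted at follow-up: 100% - 25% = 75%. Debuts before baseline as a share of all debuts: 7/25 = 28%. The analytic sample also reproduces: 46 schools x 140 = 6440. Age at debut has no sample size or power figure of its own.

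**Assumptions (not in the documents).** Hazard of debut after baseline multiplied by 0.64 in the intervention arm; age 12.75 or 13.0 at baseline and 15.6 at follow-up; mean age of pre-baseline debut 11.75, 12.0 or 12.25; hazard constant or rising linearly. That makes 12 combinations.

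**Debuts after baseline.** Control: 0.93 - 0.75 = 18.0%. Intervention: 0.93 x [1 - (0.75/0.93)^0.64] = 12.0%. The pre-baseline share of debuters rises from 28% to 0.07/(0.07 + 0.1196) = 37%.

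**Mean age among all debuters** = (0.07 x pre-baseline mean + p x post-baseline mean)/(0.07 + p), where p is the proportion debuting after baseline.

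- Smallest shift (constant hazard, baseline age 12.75, pre-baseline mean 12.25). Control: (0.07 x 12.25 + 0.18 x 14.124)/0.25 = 13.60. Intervention: (0.07 x 12.25 + 0.1196 x 14.142)/0.1896 = 13.44. Difference -1.9 months.
- Largest shift (rising hazard, baseline age 13.0, pre-baseline mean 11.75). Control 13.87, intervention 13.62. Difference -3.1 months.
- All 12 combinations are negative.

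**Post-baseline debuts only.** The difference is +0.16 to +0.22 months. A one-third fall in debuts is practically invisible.

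**Smaller effects, all debuters.** A 10% hazard reduction gives -0.4 to -0.7 months; 20% gives -0.9 to -1.4 months.

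**Other effect patterns** (baseline age 12.5, 2.75 years of follow-up, pre-baseline mean 11.5; constant, linear or quadratic hazard):

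| Pattern | Post-baseline debuts only (years) | All debuters (years) |
|---|---|---|
| Every debut delayed 0.5 years | +0.14 to +0.27 | +0.09 to -0.29 |
| Hazard halved in first 1.4 years only | +0.08 to +0.25 | +0.02 to +0.03 |
| Effect growing to a hazard ratio of 0.4 | -0.10 to -0.18 | -0.28 to -0.43 |

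**Precision, all debuters.** Per arm, 23 x 140 x 0.25 = 805 debuters, or 35 per school. With the plan's ICC of 0.015, which is set for the primary outcome, the design effect is 1 + 34 x 0.015 = 1.51. SE = SD x sqrt(2 x 1.51/805) = 0.061 x SD. An assumed SD of 1 to 2 years gives 0.06 to 0.12 years, or 0.7 to 1.5 months. A hazard ratio of 0.64 then gives a wrong-direction estimate of about 1.3 to 4.2 SEs; a 20% reduction reaches about 2 SEs only at the extreme; a 10% reduction stays below 1.

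**The alternative on the same inputs.** Among students not debuted at baseline, control 0.18/0.93 = 19.4% and intervention 0.1196/0.93 = 12.9%. Risk ratio 0.66, risk difference -6.5 percentage points: the right direction.

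**The case against.** The mean-difference rule is never tied to this outcome by name. The Background reports debut effects from the two source trials as odds ratios (0.52 and 0.55), so a yes/no coding may be intended, and that would use the binary branch without difficulty. The version table refers to a statistical analysis plan agreed in January 2023, and the analysis section to a data dictionary; neither text is in the file. This stands in part. The classification is an inference, and a reader should not conclude that the trial team deliberately chose a biased analysis. But version 7.0 was aligned with that plan, the outcome is worded as an age, and nothing in the text converts it to a binary.

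Counting pre-baseline debuts is also unstated. The primary outcome is restricted to first sex occurring after baseline; if the same restriction applies here, a constant hazard ratio hides the effect and does not reverse it. This stands, and is why both versions are shown.

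The value 0.64 mirrors the 36% target for non-competent first sex, which is a different outcome. It is an illustration only, and smaller effects give smaller distortions.

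A reader might infer that the trial would report harm if the intervention delays debut. The table above does not support that: a uniform delay or an early effect can still give a small positive difference.

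**Conclusion.** The concern holds as a should-fix point with moderate confidence. As written, the default for a numeric age is a mean among roughly a quarter of students, selected after randomisation. The estimate can hide, attenuate or reverse a true delay: about +0.2 months (post-baseline debuts only) or -1.9 to -3.1 months (all debuters) at the illustrative hazard ratio of 0.64, and -0.4 to -1.4 months (all debuters) for a 10-20% reduction. These sizes rest on the assumed ages, hazard shapes and effects. The 75% not debuted and the 7 in 25 pre-baseline debuts come from the plan's own figures.

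The primary outcome and the sample size are not affected. It would also be tempting to extend the point to non-use of contraception at first sex. The documents do not say whether that outcome counts pre-baseline debuts, and no bias has been quantified for it, so it calls only for a statement of its population.

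**What to change.** 1. For age at debut, replace the mean difference with one of the following, and name it as the estimand:
   - debut by follow-up among students not debuted at baseline, analysed as binary in the existing GEE (risk ratio and risk difference); or
   - a discrete-time or Cox model in the same students, censored at the follow-up survey, with school-clustered robust standard errors. The discrete-time form suits an age recorded in whole years; the item's resolution is not shown.
2. Set baseline debut status from the baseline survey or, where that response is missing, from the age at debut reported at follow-up, in line with the existing imputation rule.
3. State whether non-use of contraception at first sex is limited to post-baseline debuts, as the primary outcome is.

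The cost is a change of wording and a modest change to the analysis code, with no new data collection. The small downside is reliance on recalled age for endline students with no matched baseline response: 1667/6268, roughly 27%, in the Supplementary Material 4 flow diagram. A sensitivity analysis of debut by follow-up among all respondents would need no baseline status; on the illustration above it compares 25.0% with 19.0%.

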*Economic outcomes:* Outcomes for the economic analysis will include the above primary and secondary outcomes. In addition, the Child Health Utility (CHU) 9D measure(78) will be used to assess student’s health‐related quality of life. The CHU‐9D is a validated age‐appropriate measure that was explicitly developed using children’s input and has been suggested to be more appropriate and function better than other health utility measures for children and adolescents.(79) This measure performed well in the pilot. Student utility values will be collected at baseline and at follow‐up surveys at 33 months using the CHU‐9D questionnaire.

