***Assessment and follow up***

Baseline surveys will be done before randomisation when students are in year 8 (age 12/13) in November 2021-March 2022 and will collect data on socio-demographic characteristics, sexual debut and other covariates, drawing on existing survey items.(80) Consent procedures are described under ethics below. Paper questionnaires will be completed confidentially in classrooms supervised by trained fieldworkers, with teachers remaining at the front of the class to maintain quiet and order, but unable to see student responses. Previous experience indicates that paper questionnaires are acceptable and logistically more straightforward than tablet surveys. We will survey absent students by leaving questionnaires and stamped addressed envelopes with schools, and liaising with schools to maximise returns. If schools do not allow face-to-face fieldwork visits, we will instead survey students using an online survey. This will involve students completing online surveys in classrooms supervised by teachers but with teachers remaining at the front of the class to maintain quiet and order, but unable to see student responses, and with fieldworkers available via telephone or internet technology to answer questions in real time. If schools dismiss classes and move to online learning because of Covid infections, we will offer schools the option of surveying students online at home. Schools will send students details of how to log in to surveys using laptops, phones or tablets. Surveys will include links to information boxes explaining key terms informed by the questions students have raised during classroom-based surveys. Students will be asked to skip questions they do not understand or do not wish to answer. Students will be advised to contact their school safeguarding lead for support should they feel confused or upset as a result of completing the questionnaire, with the team briefing safeguarding leads about this and liaising with them to record where this has occurred. We will resurvey students at 33 months (September-December 2024) as students begin year 11 (age 15/16) and will collect self-report data on socio-demographic characteristics, intervention reach/acceptability and outcomes. Survey fieldworkers, but not students, will be blind to allocation. Based on past studies and our pilot,(51, 72, 81) we expect at least 80% survey response rates at baseline and follow-up.

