The primary analysis of all outcomes will include adjustment for stratification factors used in the randomisation. Our primary analysis will be an analysis that is adjusted for the stratification factors only. An additional adjusted analysis will be carried out which will adjust for prespecified cluster level summaries of baseline student age, gender, ethnicity and SES (as measured by the family affluence scale), imputed where feasible from baseline data if missing at follow-up. In addition, any other major imbalances observed between randomised groups will be adjusted for in exploratory secondary analyses. Interim analyses will not be conducted and will not inform intervention modification or discontinuation because this is a cluster RCT with one follow-up wave.

We will undertake exploratory tests of interaction to assess how effects are moderated, including by student gender, sexual orientation, ethnicity and SES as well as by school GCSE attainment and local deprivation (RQ2). These will be exploratory, with limited statistical power. We will also undertake complier-average causal effects analyses to examine how effects are affected by fidelity of implementation (RQ3). Economic analyses will calculate intervention costs and cost-effectiveness (RQ4) (see below). Descriptive statistics will describe fidelity, reach and acceptability using Chi-square tests to examine differences between schools. These will examine whether fidelity differs by school-level GCSE attainment and local deprivation, and whether student-level reach and acceptability differ by student-level gender, sexual orientation, ethnicity and SES. (RQ5). Quantitative and qualitative data from control schools will be analysed to describe usual treatment in control schools (RQ6). Qualitative data will also be used to develop hypotheses about implementation processes/intervention mechanisms and how these might vary between schools or students (RQ7). We will draw on all data to refine the intervention theory of change and draw conclusions about the potential for the intervention to be delivered and be effective elsewhere (RQ8).

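### No model described uses baseline sexual debut, a baseline outcome value or baseline CHU-9D, so precision and protection against chance imbalance are forgone

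*Combined protocol and SAP*

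**What the plan says.** Under Data management and analysis the primary model is fixed: "Our primary analysis will be an analysis that is adjusted for the stratification factors only". According to Recruitment and randomisation, those factors are school GCSE attainment and local deprivation. The additional analysis adjusts for "prespecified cluster level summaries of baseline student age, gender, ethnicity and SES". Any other large imbalance seen between arms is left to exploratory secondary analyses.

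More than this is collected. Under Assessment and follow up, the baseline survey "will collect data on socio-demographic characteristics, sexual debut and other covariates". Under Outcome measures (economic outcomes), "Student utility values will be collected at baseline and at" the 33-month survey. Debut is used to define the primary outcome, which counts only first sex after baseline, and missing baseline age of debut is imputed from follow-up (Study population). It enters no model as a covariate.

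Economic analyses describes a multilevel model with random intercepts and names no covariates. It defers detail to a separate economic analysis plan, which is not among the documents.

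Minimising bias describes the primary analyses as adjusted for possible imbalance at baseline. That does not fit a model adjusted for the strata alone.

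**The concern.** In a trial with about 45 schools at follow-up, most of the uncertainty in the treatment effect comes from differences between schools. A school-level baseline covariate that predicts those differences is one of the few inexpensive ways to reduce it. The share of a school's pupils already sexually active in year 8 is an obvious candidate for predicting first-sex outcomes by year 11, and the data are in hand.

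For the cost-utility analysis the point is more direct. Utility is measured only at 0 and 33 months. If QALYs are computed as an area under the curve, half the weight falls on the baseline value, and a chance difference between arms at baseline enters the QALY difference unless the model adjusts for it.

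Leaving other imbalances to exploratory analyses means that those covariates would be chosen after the imbalance has been seen. Naming them in advance avoids that.

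**Working it through.** **1. The plan's power.** Inputs from Analytic sample and sample size: "for 80% power with 5% significance, conservatively assuming: a sample of 140 students per school; drop out of 2 schools per arm" (so k = 23 schools per arm, m = 140); "80% student survey response rate at follow-up"; "an intra-cluster correlation coefficient (ICC) of 0.015 for our primary outcome"; "prevalence of this outcome of 9% among those in the control arm"; and 5.85% in the intervention arm. A two-sided 5% test is assumed.

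Variance of the risk difference = [p1(1−p1) + p2(1−p2)] × [(1−ICC)/m + ICC] / k
= (0.0819 + 0.0551) × (0.00704 + 0.015) / 23 = 0.000131, so SE = 0.01146.

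z = 0.0315 / 0.01146 = 2.75, and power = Φ(2.75 − 1.96) = **78.5%**. A full 36% reduction (5.76%) gives 81.0%. The stated 80% is therefore reproduced, with no covariates, when 140 is the number analysed per school (46 × 140 = 6440). If the 80% response is applied on top (m = 112), power at 5.85% is 75.4%.

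**2. Where the variance lies.** The design effect is 1 + 139 × 0.015 = 3.085, of which m × ICC = 2.1 is between schools: 2.1/3.085 = 68%. This is a share of the variance of the effect estimate. Of the outcome variance itself, 1.5% is between schools.

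**3. Effect of a school-level covariate.** Let r be the correlation of school baseline debut prevalence with the school effect, after the strata. Replace ICC in the second bracket by ICC(1 − r²). The documents give no value of r, so a range is shown (m = 140, 5.85%):

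| r (assumed) | Fall in variance, r² × 0.68 | Power |
|---|---|---|
| 0 | 0% | 78.5% |
| 0.1 | 0.7% | 78.8% |
| 0.2 | 2.7% | 79.6% |
| 0.3 | 6.1% | 81.0% |
| 0.5 | 17.0% | 85.5% |
| 0.7 | 33.4% | 92.0% |

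At m = 112 the values for r = 0, 0.3 and 0.5 are 75.4%, 77.8% and 82.2%.

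**4. Student-level debut would not do the same.** Suppose 7% are sexually active at baseline (the plan's figure for 12-13 year-olds) and so cannot have the outcome. Then R² = 0.07 × 0.93 × (0.09/0.93)² / (0.09 × 0.91) = 0.0074, and power rises by only 0.1 to 0.3 points. Student-level adjustment would also lose, or have to impute, the endline students with no matched baseline record: 1667/6268 = 26.6% (Supplementary Material 4).

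**5. QALYs.** Assume area under the curve with linear interpolation over 33/12 = 2.75 years. A baseline utility difference d then adds d × 2.75/2 = 1.375d to the QALY difference.

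The SE of d is SD × √{Σ over arms of [1 + (n/k − 1) × ICC]/n}, with n = 3578 in 24 schools and n = 3392 in 25 schools (Supplementary Material 4). SD and ICC are assumed:

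- SD 0.10, ICC 0.01: SE 0.0037, 95% range ±0.007, hence ±0.010 QALY per student.
- SD 0.15, ICC 0.03: SE 0.0082, 95% range ±0.016, hence ±0.022 QALY per student.

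If baseline and follow-up utility correlate ρ, with equal SDs, the carry-over is larger by a factor (1 + ρ).

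**The case against.** Adjusting for the stratification factors alone is a valid prespecified choice, and the plan regards those factors as key predictors of sexual health. The version table says the protocol was aligned with an analysis plan agreed with the DMEC in January 2023. Unused efficiency is not an error. All of this stands.

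The size of the power gain is also open to doubt:

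- r must be net of GCSE attainment and deprivation, which may already take up much of the between-school variation.
- A school prevalence from about 140 students is noisy. If debut also had an ICC of 0.015 (assumed), its reliability would be 2.1/3.085 = 0.68. An observed r of 0.5 would then need a true correlation of about 0.61, and 0.7 about 0.85.
- The ethics section lists sex before age 13 among the disclosures that breach confidentiality, and baseline students are 12 or 13. Under-reporting is a plausible inference and would weaken the covariate.

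These points make 0.7 optimistic and are why the conclusion rests on 0.3 to 0.5 or less. They do not remove the case for a covariate that costs so little.

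The primary outcome has no baseline value of its own, so adjusting for baseline outcome cannot apply to it. For the other outcomes, the documents do not list which scales were measured at baseline. The student needs survey draws on the baseline survey and gives knowledge gaps and risk behaviours as examples, which is only indirect evidence. That part of the recommendation is therefore conditional.

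On QALYs, a reader might infer that the economic analysis will ignore baseline utility. The documents do not support that: the section is a summary, it does not state an area-under-the-curve method, and it defers to a plan not supplied. What stands is that the text available does not name the adjustment.

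**Conclusion.** The point holds as an improvement the trial can make with data it already has. Neither statistical model includes baseline debut or any baseline outcome value, and the economic section names no adjustment for baseline utility.

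Two stronger readings are tempting, and neither is supported. One is that the unadjusted estimates are biased: randomisation makes them unbiased on average, and the issue is chance imbalance and precision. The other is that the trial misses its planned power through this choice: the 80% figure was derived without covariates and reproduces on that basis.

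The gain on the primary outcome is from about 78.5% power to between 81.0% and 85.5% if r is 0.3 to 0.5 after the strata, and under about 1 point if r is 0.1 to 0.2. For QALYs, unadjusted chance imbalance could plausibly shift the difference by ±0.010 to ±0.022 per student, given the assumed SD, ICC and area-under-the-curve calculation. The internal conflict between Minimising bias and the strata-only sentence needs no assumption.

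**What to change.** 1. Add school-level baseline prevalence of sexual debut to the prespecified adjusted model in Data management and analysis. Put it in the primary model only if that is fixed before outcome data are seen. Supplementary Material 4 already reports endline response, so the change should be dated and the state of data access recorded.
2. For each continuous outcome that was measured at baseline, list it and add the school baseline mean. A school mean keeps the 26.6% of endline students with no matched record.
3. State, in Economic analyses or the economic analysis plan, that QALYs are adjusted for baseline CHU-9D in the multilevel model. If that plan already says so, a cross-reference is enough.
4. Reconcile Minimising bias with the strata-only sentence, so that it is clear which analysis adjusts for what.

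The cost is wording in two plans and about one cluster-level degree of freedom per covariate, out of about 45 schools (23 control and 22 intervention at endline). No new data are needed.
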